### Sample size

The main aim of the trial is to assess if any of the enhanced practice support arms (site visit, educational outreach, or both) improved ABCS CQM outcome performance relative to practices that received PF alone. If one assumes a 20 % attrition rate over the life of the study leaving 50 practices in each of the four intervention arms, we have 80 % power to detect a 0.114 proportion improvement in any of the three enhanced practice support arms relative to PF for the 1-year practice outcomes blood pressure CQM or aspirin CQM. We assumed an outcome standard deviation of 0.26 for both ABCS outcomes (based on baseline data from the enrolled practices) and a *F* test comparing the four intervention arms assessing for any difference between groups. Further, we used an adjusted sample size calculation for ANCOVA models [29] (proposed analysis adjusts for baseline outcome) assuming a 0.60 correlation coefficient between baseline outcome measure and follow-up outcome measure. Even with an additional 10 % clinic attrition rate (45 practices per arm with follow-up), we will have 80 % power to detect a difference of 0.121 in practice proportion improved in either ABCS outcome. We conducted power calculations via simulation using R version 3.0.2.

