Three specific external practice support strategies stand out as promising approaches to build QI capacity in primary care: practice facilitation (PF), shared learning opportunities, and educational outreach [7]. PF is delivered by a facilitator, usually external to the practice setting, who enables those who work within a practice to implement a change in care delivery [9]. It is a guided interactional process that has great potential and demonstrated ability to support uptake and application of scientific knowledge to improve clinical and managerial decision-making [10]. There is substantial evidence for the effectiveness of PF to support improvement in primary care settings [11, 12]. Shared learning opportunities, such as the learning collaborative approach pioneered by the Institute for Healthcare Improvement, can motivate change [13]. Educational outreach, often called academic detailing, involves a trained outside expert delivering one or more educational messages to a healthcare professional or the clinical team. It is generally considered a promising method of modifying health professional behavior, with a 5.6 % average improvement in guideline concordant behavior from one large systematic review [14].

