## Methods

### Study setting and recruitment

The study is taking place from May of 2015 to April of 2018 in smaller primary care practices across three states: Washington, Oregon, and Idaho. H2N is a collaborative partnership between the MacColl Center for Healthcare Innovation at the Group Health Research Institute, Qualis Health in Washington and Idaho, the Oregon Rural Practice Research Network (ORPRN) based at the Oregon Health Sciences University, and the University of Washington’s Institute of Translational Health Sciences. Qualis Health is recruiting practices and providing PF support in Washington and Idaho. ORPRN is recruiting practices and providing PF support in Oregon. The recruitment goal is 250 practices: 120 in Washington, 100 in Oregon, and 30 in Idaho. To be eligible, practices must have 10 full-time or fewer providers in a single location and meet stage 1 electronic health record (EHR) meaningful use criteria. Our rationale for these priority criteria is to focus efforts on smaller practices with the greatest need for externally provided QI expertise and have some capability to produce clinical performance measure reports at the start of the study, given the relatively short 36 months of funding.

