### Study design

A two-by-two factorial design is being used to compare the effectiveness of adding shared learning opportunities and educational outreach to PF. (Fig. 1) The four factors (intervention arms) are (1) PF alone, (2) PF and shared learning, (3) PF and educational outreach, and (4) PF combined with both shared learning and educational outreach. In addition, a set of control data for the ABCS clinical performance measures will be obtained from a randomly selected national sample of primary care practices not participating in the study. This control data will consist of the four ABCS clinical performance measures over the same historical time period and reporting intervals as the practices enrolled in the H2N study. Control practices will be matched on practice size (clinician FTE), QI measure reporting capabilities, and rural/urban location. This data will be provided by the DARTNet Institute [15].

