**Fig. 2 Fig2:**
[figure not shown]
Project timeline and data collection windows

For the primary analysis to assess differences between the four intervention groups on the primary outcome practice-level proportion with blood pressure control at 1-year follow-up (blood pressure CQM), we will fit the following linear regression model:$$ {Y}_i={\beta}_0+{\beta}_1{X}_{1i}+{\beta}_2{X}_{2i}+{\beta}_3{X}_{3i}+{\beta}_{\mathrm{base}}{Y}_i^0+{\boldsymbol{\beta}}_z{\boldsymbol{Z}}_{\boldsymbol{i}}+{e}_i\ {e}_i\sim N\left(0,{\sigma}^2\right)\ i=1,\dots, N $$where *Y*
_*i*_ is clinics *i* blood pressure CQM at 1-year follow-up, *X*
_1*i*_, *X*
_2*i*_, and, *X*
_3*i*_ are three indicator variables for intervention assignment for site visit, educational outreach, or both, respectively, *Y*
_*i*_^0^ is baseline blood pressure CQM, and ***Z***
_***i***_ is a vector of other baseline covariates to adjust for differences between clinics including PF support organization (Qualis Health or ORPRN), baseline prior practice experience obtaining customized data to drive improvement (yes, no), and baseline prioritization of the work by the practice (high, low). We will use the Fisher’s protected least significant difference approach to control for multiple comparisons due to the comparison of four intervention arms. Specifically, we will first calculate an Omnibus *F* test to assess if there are any significant differences between intervention groups and only calculate pairwise comparisons if this omnibus test is statistically significant.

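### The stated 80% power for a 0.114 gain over PF is the power of the omnibus F test; the planned two-step comparison of a given enhanced arm with PF has about 71–76%, and never more than 78%

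*Protocol article*

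**What the plan says.** The Sample size section of the protocol article gives the main aim as finding out whether any enhanced arm (site visit, educational outreach, or both) did better than PF alone. With attrition of 20% "leaving 50 practices in each of the four intervention arms", it claims 80% "power to detect a 0.114 proportion improvement in any of the three enhanced practice support arms relative to PF". It adds that with 45 practices per arm the detectable difference is 0.121.

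The same section names the test behind these figures, an F "test comparing the four intervention arms assessing for any difference between groups". It gives an SD of 0.26 and a baseline to follow-up correlation of 0.60. It does not state alpha or the assumed means of the other arms.

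The Data analysis section fits three arm indicators and applies Fisher's protected LSD. The analysts will "only calculate pairwise comparisons if this omnibus test is statistically significant".

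**The concern.** The claim and the calculation refer to different events. The claim is about an improvement over PF. The calculation counts every trial in which the F test rejects equality of the four arms, including trials in which no enhanced arm is then shown to beat PF. Under the plan, a finding against PF needs both steps, and the power for both is not reported.

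This affects how the results will be read. A reader who sees a non-significant comparison of, say, the outreach arm with PF will set it against a stated 80% chance of detecting 0.114. If the planned procedure had a lower chance than that, the null result will be given too much weight.

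**Working it through.** **Inputs.** "The recruitment goal is 250 practices" (Study setting and recruitment), so 250 × 0.8 / 4 = 50 per arm. "We assumed an outcome standard deviation of 0.26 for both ABCS outcomes", with correlation 0.60 (Sample size). Alpha is assumed to be 0.05 for the F test and two-sided 0.05 for each pairwise test.

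**Residual SD after baseline adjustment.** 0.26 × √(1 − 0.60²) = 0.26 × 0.80 = 0.208, variance 0.043264.

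**Reproducing the stated figures.** The F test has 3 and 4n − 5 df and noncentrality λ = n × Σ(μ − mean)² / 0.043264. If one arm is raised by δ, Σ(μ − mean)² = 0.75 δ².

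- n = 50, δ = 0.114: λ = 50 × 0.75 × 0.012996 / 0.043264 = 11.27, power 0.8055.
- n = 45, δ = 0.121: λ = 45 × 0.75 × 0.014641 / 0.043264 = 11.42, power 0.8105.

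The differences giving exactly 80% are 0.1133 and 0.1195. Without the baseline adjustment the powers would be 59–60%. The published figures are therefore omnibus F-test figures with the adjustment, and they fit alpha 0.05 and one arm differing from three equal arms.

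**Upper limit for one arm against PF.** The standard error of a pairwise difference is 0.208 × √(2/50) = 0.0416, and 0.114 / 0.0416 = 2.74. The ungated two-sided t test has 78% power. Requiring a significant F test first can only lower this.

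**Two-step power at 0.114, n = 50.** Success means that F is significant and the arm is significantly better than PF (400,000 simulated trials per pattern). With nδ²/SD² = 15.02, λ is 15.02 times the multiplier shown.

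| Enhanced arms raised | λ | F test | Named raised arm vs PF | At least one arm vs PF |
|---|---|---|---|---|
| One by 0.114 | 0.75 × 15.02 = 11.27 | 81% | 71% | 71% |
| Two by 0.114 | 1.00 × 15.02 = 15.02 | 91% | 76% | 86% |
| Three by 0.114 | 0.75 × 15.02 = 11.27 | 81% | 71% | 81% |
| Singles 0.057, both 0.114 | 0.50 × 15.02 = 7.51 | 61% | 60% (combined arm) | 61% |
| Singles 0.114, both 0.228 | 2.00 × 15.02 = 30.04 | 99.8% | 78% (each single arm) | 99.8% |

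With one arm raised, F is significant but that arm is not shown better than PF in about 81 − 71 ≈ 9% of trials before rounding (80.6 − 71.4). These count as successes in the published 80%.

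**Fallback scenario.** At n = 45 and 0.121 with one arm raised: F 81%, named arm against PF 72%.

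**Difference needed for 80% two-step power, one arm raised.** Power is 76.5% at 0.120 and 81.1% at 0.126. Interpolating, 0.120 + 0.006 × (80 − 76.5)/(81.1 − 76.5) ≈ 0.125.

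**Factorial main effects.** The standard error for 100 against 100 is 0.208 × √(2/100) = 0.0294. With only the combined arm raised, all three raised, or the half-effect additive pattern, each main effect is 0.057. Then 0.057 / 0.0294 = 1.94 and power is 49%. If one component adds 0.114 whether or not the other is present, 0.114 / 0.0294 = 3.88 and power is 97%, against 76% for the planned comparison.

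**The case against.** The best defence is that nothing is miscalculated or hidden: the figures reproduce, and the section says that an F test across four arms was powered. The aim is also worded as any enhanced arm, so the power for at least one arm to beat PF is a legitimate reading. That reading meets 80% when three arms improve (81%) or two do (86%). Both points stand. But it falls to 71% with one arm improved, which is the natural pattern behind the published figure, and the text does not say which pattern it assumes.

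Three stronger readings are tempting, and the documents support none of them.

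- A reader might infer that the 80% holds in only one pattern of means. It does not: omnibus power is 81% with one or three arms raised and 91% with two.
- A reader might infer that the planned test delivers 60–71% in general. The 60% needs a pattern in which each component adds half of 0.114. The article never states additivity, and two of the three arms then gain less than the difference in the claim.
- The Study design section says "A two-by-two factorial design is being used to compare the effectiveness of adding shared learning opportunities and educational outreach to PF", so a reader might infer that factorial contrasts would recover the lost power. They do not in the one-arm, three-arm or half-effect additive patterns (49% or less each; a joint 2-df test of both main effects has 68% with only the combined arm raised, all three raised, or the half-effect pattern). If both single arms work and the combination does not, the main effects are zero while the plan has 86% for at least one arm. Main effects gain clearly when a component works with or without the other. They also average over the other factor, which is a different question from an arm against PF alone.

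A fuller protocol or SAP may report pairwise power. That would not correct the sentence published here.

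**Conclusion.** The point holds in a limited form. The 80% is correct for the omnibus F test and is attached to the wrong conclusion. For a named enhanced arm against PF at 0.114, the planned procedure has 71% power (one or three arms raised) or 76% (two raised), and at most 78% whatever the other means are. For at least one arm against PF it has 71%, 86% or 81% with one, two or three arms raised, and about 61% if only the combined arm reaches 0.114 with each component adding half. The 45-per-arm statement is affected in the same way.

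These figures rest on the article's SD and correlation, equal arms, normal errors and an assumed alpha of 0.05, which the reproduction of both published figures supports. The pattern of means is an assumption throughout, so a range is given. This is a mislabelled power statement, not an arithmetic error or a flaw in the test procedure.

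**What to change.** In the Sample size section, state alpha and the assumed pattern of means. Say that 0.114 (50 per arm) and 0.121 (45 per arm) are detectable differences for the omnibus F test when one arm differs from three equal arms. Then add the power of the planned comparison with PF, F test and pairwise test together: about 71% at 0.114 (72% at 0.121 with 45 per arm), with about 0.125 needed for 80% at 50 per arm when one arm is raised. If the at-least-one-arm reading is intended, say so and give 71%, 86% and 81% for one, two and three arms raised.

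Optionally, report the two main-effect contrasts and the interaction with its interval as supplementary estimates from the model already fitted. They should not be presented as the remedy for the power gap.

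The cost is a few sentences and a less favourable stated power. No practices, data or changes to the primary test are needed.

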### Trial status

At the time of manuscript submission, the study was 16 months into the 36 months of support from AHRQ. The Group Health Research Institute’s Institutional Review Board approved this study.

## Discussion

### Significance

While prior research identified promising approaches for supporting primary care practice improvement in the USA, there have been few comparative effectiveness studies that rigorously assessed the combinations of the external practice support interventions described here. In a study that compared traditional learning collaborative with PF to PF alone, the addition of a local learning collaborative enhanced use of asthma guidelines [30]. In addition, little is known about effective and efficient approaches to support practice improvement across a large geographic region with the number and diversity of smaller primary care practices enrolled in Healthy Hearts Northwest [31, 32].

Evaluations of the effectiveness of the traditional “learning collaborative” approach to shared learning have shown mixed results [33, 34]. Our unique approach to shared learning through site visits is grounded in diffusion of innovation theory on the premise that such visits create opportunity to more directly observe QI approaches and understand how these can be adapted to a practice’s own circumstances and setting [35]. Site visits may also serve to alter informal peer social networks by establishing or strengthening ties between individuals across practices or clinics [36]. In one of the few studies of the influence of a social network, Keating and colleagues demonstrated that physicians were more likely to obtain information from colleagues with greater expertise and experience [37].

The role of educational outreach in addition to practice facilitation and or shared learning activities is largely unknown. Traditional educational outreach is a one-on-one activity between an academic expert and an individual clinician. In a study of group versus individual academic detailing for use of antihypertensive medications, both were equally more effective than usual care practices in improving prescribing habits [38]. For purposes of this study, we will be using educational outreach to help facilitate a major shift in the way that the clinicians and their teams approach all four ABCS risk factors by combining them into a single CVD risk measure. The alternative is to conduct educational outreach for each individual ABCS measure separately. If successful, this shift in approach would be a significant step forward in implementation methods.

### Limitations

In addition to recruitment and retention barriers, potential limitations to building the QI capacity include a lack of EHR resources needed to generate ABCS clinical performance measures even though the system may meet stage 1 EHR meaningful use criteria, no financial incentives for investing in building QI capacity, and the competing demands of the changing reimbursement environment such as implementation of the Medicare Access and CHIP Reauthorization Act [39]. In addition, disruptions such as implementing a new EHR, turnover in practice leadership, changes in practice staffing, or practice acquisition by a larger healthcare organization pose significant barriers to building high-functioning QI teams. We will mitigate EHR limitations by providing specific consultations and technical assistance by information technology experts from both Qualis Health and the Oregon Health Sciences University. Practice facilitators will work closely with their assigned practices to assess additional opportunities to participate in other practice transformation support initiative and assess their synergy with the Healthy Hearts Northwest support as well as maintaining trusting relationships with all members of the practice team to assist them with disruptions when they occur.

### Impact

In addition to its impact on CVD across a large population in the Pacific Northwest, the work of improving the capacity of smaller practices to engage in QI activities will prepare them for the transition to value-based reimbursement. Our findings will also have broad implications for understanding the type of technical assistance and support required to support smaller primary care practices in a rapidly changing healthcare environment.

## Abbreviations

ABCS: Aspirin, blood pressure, cholesterol, smoking
AHRQ: Agency for Healthcare Research and Quality
CPCQ: Change Process Capacity Questionnaire
CVD: Cardiovascular disease
EHR: Electronic health record
H2N: Healthy Hearts Northwest
LDL: Low-density lipoprotein
NQF: National Quality Forum
ORPRN: Oregon Rural Practice Research Network
PF: Practice facilitation
QI: Quality improvement
QICA: Quality improvement capacity assessment
USA: United States of America
